### Interventions

#### Experimental groups

The experimental groups will be provided with a defatted almond protein powder (Provided by Harris Woolf Almonds; California, United States of America) as part of their dietary intervention. They will be asked to consume this supplement once daily with their usual breakfast and additionally after each supervised training session (2 days per week). For the daily serving, participants will be instructed to mix a pre-packaged single-dose unit with 250 ml of provided almond milk and chocolate powder (the total drink providing: 1127.6 Kj, 18.3 g protein, 28.2 g carbohydrate, 7.0 g fat and 8.2 g fibre; see appendix 4). This shake will be consumed with breakfast, as breakfast is typically suboptimal for protein for this demographic [19]. On training days, participants will consume a larger post-exercise serving consisting of 56 g of defatted almond meal and 300 ml of almond milk and 30 g of chocolate powder, providing a total of 1724.4 kJ, 29.4 g protein, 43.1 g carbohydrates and 13.0 g fibre. Details of the supplement and placebo compositions are provided in Appendix 4.

Participants in the placebo group will be provided an energy-matched maltodextrin drink to consume for breakfast and post training also mixed with provided almond milk (See Appendix 4). Maltodextrin was selected as the placebo comparator as it can be easily energy-matched without including other confounding nutrients (e.g., protein, fat or fibre). Once prepared with almond milk, both the intervention and placebo drinks are similar in appearance, colour, and volume, presenting as a light, opaque beverage. While minor differences in texture or mouthfeel may be perceptible due to the differing nutrient composition, participants are not informed of these differences, and no information is provided that would enable identification of group allocation.

### Resistance and high-intensity training session

The supervised training intervention will commence in Week 2 of the study and continue for the full intervention period (10-weeks in total). Participants will attend two supervised training sessions per week on non-consecutive days, with a minimum of 48 h between sessions to allow for recovery. Each participant will train at a consistent time of day throughout the study, selecting either a morning session (7:00–9:00 AM) or afternoon session (2:00–5:00 PM) based on availability and preference. All training sessions will be fully supervised by either an accredited exercise physiologist or a certified personal trainer to ensure correct technique, monitor safety, and provide standardised instruction across sessions.

The resistance training protocol employed in this study is informed by the American College of Sports Medicine (ACSM) position stand on progressive resistance training for older adults and is designed to elicit improvements in skeletal muscle mass, strength, and functional capacity [50]. Comparable protocols have consistently demonstrated efficacy in enhancing muscle hypertrophy, neuromuscular performance, and physical function in older populations [12, 50].

Each training session will comprise six exercises, with the specific movements alternating across two distinct sessions (Table 1). All exercises will be performed using a controlled 2-1-2 repetition tempo (2 s eccentric, 1-second pause, 2 s concentric) to increase time under tension and promote motor control. Standardised rest intervals of 60–90 s between sets, and 2–3 min will be allotted between exercises (Tables 1 and 2).

**Table 1 Tab1:** Outline of resistance exercise protocol

Session 1	Session 2
1. Leg press	1. Leg press
2. Seated leg curl	2. Seated leg curl
3. Leg extensions	3. Leg extensions
4. Seated row	4. Lat pulldown
5. Machine chest press	5. Machine chest-press
6. Standing DB shoulder press	6. Seated DB shoulder press

Notes:

• Exercises performed at 2-1-2 tempo (ECC – ISO – CON)

• Rest 60–90 s between each set

• Rest 2–3 min between each exercise

**Table 2 Tab2:** Outline of progression of sets, reps and intensity of resistance training protocol

	Sets	Reps	Intensity
Weeks 1–2	2	10–12	65–70% 1RM or 1–2 RIR
Weeks 3–4	3	10–12	70–75% 1RM or 1–2 RIR
Weeks 5–6	3	8–10	75–80% 1RM or 1–2 RIR
Weeks 7–8	4	8–10	75–80% 1RM or 1–2 RIR
Weeks 9–10	4	10–12	70–75% 1RM or 1–2 RIR

Training loads for the leg press and machine chest press will be prescribed based on each participant’s 3-RM, assessed during the pre-intervention testing [58]. For the remaining exercises, loads will be estimated and adjusted according to participant performance and feedback using estimated 1-RM and Repetitions in Reserve (RIR)-based progression. RIR reflects the number of repetitions a participant estimates they could have completed beyond the final repetition of a set, before reaching muscular failure. For example, a RIR of 1 means the participant believes they could have performed one additional reps with proper form. This method allows for a practical and individualised approach to adjusting training intensity, helping to ensure that each participant trains within a consistent and safe effort range [59]. Loads will be adjusted throughout the intervention to maintain the target RIR range and optimise training stimulus. Two weekly sessions of resistance training, consisting of multi-joint and full-body compound exercises at moderate intensity (e.g., 60–70% 1-RM), are sufficient to promote moderate yet significant increases in muscle mass in postmenopausal women [60].

#### HIIT protocol

The HIIT protocol was adapted from previous training studies in postmenopausal women that prescribed cycling intensity between 75 and 110% of PPO in overweight or obese women and ranged in duration for 3–12 weeks [61–63]. The HIIT protocol will be performed on a cycle ergometer which is outlined in Table 3. Each session begins with a 3-minute warm-up at 20 W, followed by 10 alternating bouts of high-intensity and recovery intervals. Each high-intensity interval consists of 60 s of cycling at 70–90% of the participant’s estimated peak power output, followed by 60 s of recovery. A 2-minute cool-down at 20 W concludes the session. Work intensity will progress every two weeks, beginning at 70% of PPO in Weeks 1–2 and increasing incrementally to 90% PPO by Weeks 9–10.

**Table 3 Tab3:** HIIT protocol structure

Warm-up	3 min @ 20 W
HIIT intervals	10 × (60 s @ 70–90% PPO, 60 s active recovery)
Cool-down	2 min @ 20 W
Progression	70% PPO (Weeks 1–2) → 90% PPO (Weeks 9–10) *increasing by 5% each two weeks

#### Concomitant care

Participants will be instructed to maintain their habitual diet and physical activity patterns outside of the supervised training sessions for the duration of the study. Initiation of new structured exercise, high-intensity training or formal dietary interventions (e.g., weight loss programs, protein or fibre supplements) outside of the prescribed intervention will also be discouraged. Usual medical care and medications for unrelated health conditions will be permitted, provided they are stable for at least 3 months prior to enrolment and remain unchanged during the study period.

### Randomisation and blinding

#### Sequence generation

The random allocation sequence will be generated by an independent researcher not otherwise involved in participant enrolment, intervention delivery, or outcome assessment. A stratified block randomised approach will be used. Participants who meet inclusion criteria and consent to participate will be randomly allocated to either the experimental or placebo group after the first laboratory visit.

Randomisation will be stratified according to the following variables:

Hormone replacement therapy use (Yes/No)Appendicular skeletal muscle mass Index (Low/High), determined by baseline DXA scan and classified according to the European Working Group on Sarcopenia in Older People (EWGSOP) cut-offs [9]

#### Allocation concealment and blinding

Allocation will be concealed using the independently generated randomisation schedule. Participants, intervention providers (exercise supervisors), outcome assessors, and data analysts will be blinded to group allocation throughout the study. The intervention (defatted almond protein powder) and placebo (maltodextrin) supplements will be identical in appearance, packaging, and flavour (chocolate).

Blinding will be maintained until data collection is complete and the primary analysis has been finalised. Emergency unblinding will only occur if required for participant safety, as determined by the Chief Investigator. For further blinding participants will be asked to refrain from discussing their supplements to the assessors or other participants during the study.

### Data collection, management, and analysis

#### Data collection and management

All data collected will be undertaken by trained researchers that are familiar with the study protocols. Training will include standardisation of measurement techniques, use of calibrated equipment, and administration of questionnaires to minimise inter-assessor variability. Where applicable, duplicate measurements will be taken (e.g., blood glucose) and the average recorded. Objective outcomes include DXA-derived body composition, OGTT-derived glucose and insulin responses, blood lipids, muscle strength (3-RM testing and hand grip dynamometry), and cardiorespiratory fitness (submaximal cycle test). Subjective outcomes include validated appetite visual analogue scales and supplement acceptability questionnaires administered via REDCap. Dietary intake will be assessed using 3-day food diaries recorded via the Easy Diet Diary app and analysed using FoodWorks software. All instruments and procedures are described in detail within the Methods section and relevant appendices.

#### Data monitoring

Research assistants that are blinded to the supplement allocation will be trained on how to collect data. Data for body composition, OGTT (blood glucose) and exercise testing will be collected at the same location during the study period. Data will be collected using de-identified, participant coded data collection sheets. These data will then be transferred electronically on password protected computers and the data sheets are stored in a locked filing cabinet.

While data is being collected, all data will be checked for omissions or errors by the project manager who will maintain a data diary of any issues that arise with the data. The data then will be checked again by the principal investigator (PI) and statistician prior to any analysis. The information collected from this study will be kept until the end of the project and then placed in archives for a minimum of 5 years from the final publication of the findings. Upon completion of the study all the data will be transferred to the Deakin Research Data Store, where all data will be de-identified and may be used for future studies.

The data will remain de-identified, with only the principal investigator retaining the coding file necessary for participant re-identification. Future access to the data will require permission from the PI, who will provide access to de-identified data files on the RDS. Any new research projects utilising this data will be submitted for ethical approval by the relevant university committee. Participants will be informed of the potential for their data to be used in future projects through the Plain Language Statement, with assurance that only de-identified data will be shared with other research team members.

#### Data analysis

Participant withdrawals and missing data will be documented, with primary analyses conducted under an intention-to-treat (ITT) framework and secondary per-protocol analyses based on predefined adherence criteria. A secondary, per-protocol analysis will be carried out to include only participants that attend ≥ 80% of their training sessions and consumed ≥ 80% of their supplement over the course of the study. Between-group comparisons will be conducted using linear models, adjusting for baseline values. Outcome variables will be log-transformed where necessary to meet the assumptions of parametric testing. Within-group changes will be evaluated using appropriate statistical tests, such as mixed-models. All statistical analyses will be two-tailed, with significance set at *p* < .05. Multiple imputation by chained equations will be used to handle missing data.

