### Primary outcomes: body composition

The primary outcomes will be the mean percentage change (± standard deviation, SD) in total body and regional lean (arms and legs) and fat-free mass (FFM), assessed using DXA (Lunar Corp., Madison, WI). All DXA scans will be conducted by trained personnel experienced in the use of DXA technology and certified in accordance with standard operating procedures for body composition analysis. In addition to lean mass, total (kg) and relative (%) fat mass and visceral fat mass will also be reported as will the delta changes from pre-post training.

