#### Sample size and statistical power

As no established minimal clinically important difference exists for fat-free mass (FFM) or lean mass, as an alternative, sample size was justified on several factors: (1) based on biological aging trajectories; older adults typically experience a decline of approximately 0.5–1.0 kg per year in FFM [64, 65], equating to an estimated 1–2% annual loss. A 2.0% increase in lean mass in the intervention group may therefore be interpreted as a reversal of two years’ worth of age-related muscle loss; (2) in similar studies in this age group, the non-supplemented group may see a non-significant improvement of their lean mass of ~ 0.2–0.4% following 12-24-weeks of resistance training [66], whilst the intervention group supplemented with protein may improve lean mass by a magnitude of 2.4% [67]. Similarly, our own data with strength training 2x week in women supplemented with protein demonstrated an increase in lean mass of 2.7% [44]. The study was therefore powered to detect a between-group difference of 2.0% in FFM change (control: 0.4%; supplemented: 2.4%). Assuming a standard deviation of 2.2% (calculated from raw data from [name], Silver [44], this requires a sample size of 42 participants (21 per group) to achieve 80% power at a at α = 0.05 and accounting for an anticipated 10% dropout rate we will aim to recruit 48 participants in total.

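### The stated between-group model does not include the two stratification factors; if they are prognostic, the test is mildly conservative and a few points of power are forgone

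*Protocol article*

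**What the plan says.** Under Sequence generation, the Protocol article states: "A stratified block randomised approach will be used". It continues "Randomisation will be stratified according to the following variables" and lists two factors: hormone replacement therapy (yes or no) and appendicular skeletal muscle mass index (low or high), the latter taken from the baseline DXA scan. That makes four strata. The block size is not given.

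Under Data analysis, the model for comparing the arms is: "Between-group comparisons will be conducted using linear models, adjusting for baseline values". The natural reading is the baseline value of each outcome. The stratification factors are not mentioned there. The abstract speaks only of linear regression and mixed-effects models, and no other section adds the factors. The same Data analysis section provides for multiple imputation by chained equations without naming the variables in the imputation model.

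Under Sample size and statistical power, the calculation is a plain two-group comparison that takes no credit for covariates: a difference of 2.0 percentage points, SD 2.2%, 21 per group for 80% power, and 48 recruited.

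**The concern.** Stratified randomisation makes the arms alike on the stratification factors. If those factors are related to the outcome, the treatment estimate varies less from trial to trial than it would under simple randomisation. A model without the factors does not register that gain: the variation they explain stays in the residual, so the standard error is larger than the true sampling error. Confidence intervals are then too wide, the real type I error falls below the nominal 5%, and power is lower than the same data could give.

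With 48 women recruited, even a modest gain in precision is worth having, and both variables are recorded for every participant by the time she is randomised. The document fixes a covariate set that does not follow its own randomisation, so this is more than an absent detail.

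**Working it through.** **Inputs from the Protocol article.** Difference 2.0 percentage points, SD 2.2, two-sided α 0.05, 21 per arm evaluable, 10% dropout, 48 recruited; two binary stratification factors.

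**Assumptions, because the documents give no figure.** R² is the share of outcome variance explained by the two factors together; range 0 to 0.20. The simulation also assumes blocks of 4 and 30% prevalence for each factor.

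**Step 1: the plan's own sample size.**
- Normal approximation: n per arm = 2 × (1.96 + 0.8416)² × 2.2² / 2.0² = 2 × 7.849 × 1.21 = 18.99, so 19.
- Two-sample noncentral t: 20 per arm gives power 0.800; 21 per arm gives 0.820.
- Dropout: 21 / 0.9 = 23.3, so 24 per arm and 48 in total.

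The stated 42 and 48 are reproduced to within two participants, slightly on the safe side.

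**Step 2: idealised effect of omitting the factors.** Under perfect balance on the strata, the model standard error is too large by the factor 1/√(1−R²), and the type I error is 2 × [1 − Φ(1.96/√(1−R²))]. For the adjusted model, power at 21 per arm uses SD 2.2 × √(1−R²) and 42 − 5 = 37 degrees of freedom.

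| R² | SE too large by | Type I error, factors omitted | Power, factors included |
|---|---|---|---|
| 0 | 0% | 0.050 | 0.818 |
| 0.05 | 2.6% | 0.044 | 0.837 |
| 0.10 | 5.4% | 0.039 | 0.856 |
| 0.20 | 11.8% | 0.028 | 0.894 |

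The first two result columns are upper limits, since balance is not perfect with four strata, incomplete blocks and dropout.

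**Step 3: simulation at the planned size.** 48 women were randomised in permuted blocks within four strata, with 10% dropout and 5,000 replicates per cell. The model with baseline only was compared with baseline plus two stratum indicators. SE and type I error come from runs with no treatment effect, power from runs with a difference of 2.0.

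| R² | Baseline-only: mean model SE / true SD of estimate | Ratio | Type I error, baseline only | Power, baseline only | Power, with factors | Points forgone |
|---|---|---|---|---|---|---|
| 0 | 0.677 / 0.686 | 0.99 | 0.052 | 0.814 | 0.807 | −0.7 |
| 0.05 | 0.675 / 0.668 | 1.01 | 0.049 | 0.824 | 0.832 | 0.7 |
| 0.10 | 0.673 / 0.654 | 1.03 | 0.045 | 0.827 | 0.854 | 2.7 |
| 0.20 | 0.678 / 0.630 | 1.08 | 0.032 | 0.844 | 0.888 | 4.4 |

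With the factors in the model, type I error stayed between 0.051 and 0.054 over these rows. Monte Carlo error is about √(0.05 × 0.95 / 5000) = 0.003 for type I error, so the R² = 0.05 row cannot be told apart from no effect on that measure. A repeat with the same sample size, blocks and dropout gave standard errors 2–7% too large and 1–5 points of power forgone for R² 0.05 to 0.20.

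**Step 4: overlap with baseline lean mass.** The muscle index comes from the same scan as the primary outcome. If the low-index group is shifted by 2 SD on the baseline covariate (assumed), the points forgone become −0.6, 0.4, 1.5 and 3.9 for R² of 0, 0.05, 0.10 and 0.20.

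**The case against.** The strongest reply is that the article does not say the model adjusts for baseline values and nothing else. It excludes no covariate, it condenses a fuller document, and an analysis plan not shown may list the factors. Stratifying and adjusting for baseline are also not contradictory. This stands in part: a reader might infer that the factors have been deliberately left out, and the text does not support that. What remains is that the article does state a covariate adjustment, and as stated it does not follow the randomisation.

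A reader might also infer that the standard errors are necessarily too large. They are so only if the factors predict the outcome beyond baseline, and the documents offer no evidence on how strongly they do. At R² = 0 nothing is lost, and adding the factors costs slightly under 1 point. Choosing them as strata suggests that the trial team thought them relevant, but that is not a measured effect.

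The overlap argument has some force for the primary outcome, where baseline lean mass probably carries part of the muscle-index information. It does not cover hormone therapy, and it is weaker for lipids, glucose, strength and fitness, whose baseline values are not DXA lean-mass measures.

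Finally, the error is in the safe direction: it adds no bias and no false positives. That is correct, and it limits the weight of the point.

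**Conclusion.** The point holds in conditional form. The stated between-group model does not include the factors used to stratify randomisation. For an assumed R² of 0 to 0.20, model standard errors are about 0–8% too large, type I error runs from about 5% down to 3%, and about 0–5 points of power are forgone. The idealised figures in Step 2 of the working (up to 12% on the standard error, type I error down to 2.8%) overstate the effect for a trial of this size.

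A reader might conclude that the trial is underpowered as a result. It is not: under the plan's own difference and SD, baseline-only power was 0.81 or higher in every scenario. The loss is relative to a better analysis of the same data.

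The sizes rest on the assumed R², the assumed block size and the assumed factor prevalence. The direction does not depend on those values, provided the factors are prognostic. This is an inexpensive improvement to the model and no threat to the trial's validity.

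**What to change.** Before unblinding, state the primary model as: outcome ~ arm + baseline value of the outcome + hormone therapy (yes/no) + muscle-mass index category as randomised. Use the same terms in the secondary between-group models, and include them in the imputation model.

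If a continuous baseline muscle index is preferred to the category, make that choice now. Deciding after seeing how many women fall in the low category would let the data choose a covariate of the primary model.

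The cost is one line of analysis wording, two degrees of freedom, and under 1 point of power if the factors turn out not to be prognostic. No new data are needed. The article expects data collection to finish in October 2026 and keeps the blind until the primary analysis is final, so the terms can still be prespecified.

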#### Sample size and statistical power

As no established minimal clinically important difference exists for fat-free mass (FFM) or lean mass, as an alternative, sample size was justified on several factors: (1) based on biological aging trajectories; older adults typically experience a decline of approximately 0.5–1.0 kg per year in FFM [64, 65], equating to an estimated 1–2% annual loss. A 2.0% increase in lean mass in the intervention group may therefore be interpreted as a reversal of two years’ worth of age-related muscle loss; (2) in similar studies in this age group, the non-supplemented group may see a non-significant improvement of their lean mass of ~ 0.2–0.4% following 12-24-weeks of resistance training [66], whilst the intervention group supplemented with protein may improve lean mass by a magnitude of 2.4% [67]. Similarly, our own data with strength training 2x week in women supplemented with protein demonstrated an increase in lean mass of 2.7% [44]. The study was therefore powered to detect a between-group difference of 2.0% in FFM change (control: 0.4%; supplemented: 2.4%). Assuming a standard deviation of 2.2% (calculated from raw data from [name], Silver [44], this requires a sample size of 42 participants (21 per group) to achieve 80% power at a at α = 0.05 and accounting for an anticipated 10% dropout rate we will aim to recruit 48 participants in total.

